#### Plans to promote participant retention and complete follow-up {18b}

The RA contacts participants via telephone call (or other contact means such as emails or text messages) to complete the later stages of the follow-up questionnaires. The RA also monitors the retention rate and reasons for discontinuation of the study (e.g. consent withdrawn, lost to follow-up).

#### Data management {19}

All assessment data are entered electronically into a database (Microsoft Excel) and scanned into the Consumer Integrated Mental Health Application (CIMHA). Any publication of study results involves de-identified data only, and all study data and information are stored according to established research protocols (paper questionnaires digitised and then securely destroyed, video data stored on secure Queensland Health servers with restricted access), with research team members being supervised by experienced investigators. Participant video files are maintained in storage for a period of 5 years after completion of the study.

#### Confidentiality {27}

All participants are assigned a participation number when they consent to join the study to ensure information pertaining to their treatment and health outcomes is de-identified during analysis and reporting. All medical/mental health records kept become part of the participants’ medical records and are protected by Gold Coast Health policy (for the State of Queensland, Australia) regarding information privacy and disclosure. This is only viewable by treating clinicians accessing the participants’ medical records and is planned for routine use in clinical studies in Gold Coast Health

#### Plans for collection, laboratory evaluation, and storage of biological specimens for genetic or molecular analysis in this trial/future use {33}

This is not applicable, as no biological samples are collected.

## Statistical methods

### Statistical methods for primary and secondary outcomes {20a}

To determine the effectiveness of additional CBT + SPP or ASSIP+SPP compared with SPP alone, univariate (log rank test) and multivariate Cox proportional hazard shared frailty regression models and multilevel mixed effects parametric models will be used to analyse time to re-presentation for suicide attempts [35]. Time to suicide attempt is measured by calculating the total number of days from the initial presentation (with days of psychiatric admission for some consumers taken into account), to the re-presenting date for a subsequent suicide attempt and may include multiple representations [35]. For participants without a subsequent suicide attempt, the total number of days from enrolment to the last assessment (24 months) will be calculated. All collected demographic and clinical variables will be considered in the model-building process. Variables with *P* ≤ 0.1 on univariate analysis will be included in all combinations and retained in the model if *P* < 0.05. Plausible interactions of retained variables will be tested. Collinearity of potential model variables will be assessed using the variance inflation factor. Where appropriate, the proportional hazards assumption will be tested using Schoenfeld residuals. Kaplan-Meier plots will allow visual comparisons between the groups. Analyses will be undertaken on an intention to treat basis. Stata 15 (Stata Corp. College Station, TX, USA) will be used for statistical analyses.

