### Sample size {14}

The sample size was calculated on the basis of a time to event analysis of the time to representation for suicidality. From previous studies using CBT as an additional treatment component following attempted suicide [24, 39], we anticipated that the proportion of patients re-presenting for attempted suicide over a 2-year follow-up period will be approximately half that of the TAU group. From recent data from our health service, this represents a decrease from 48 to 24%. To detect this difference (equivalent to a hazard ratio of 0.42) by the log rank test in a proportional hazards time-to-event analysis with 80% power at a two-sided significance level of 5%, we require 132 participants in two groups of 66 each. However, we anticipated a dropout rate of approximately 4.5% per month which would result in 35% of participants completing the full 24-month follow-up (65% total dropout). The effective dropout rate is thus 41%, as those dropping out later contribute proportionately more. When accounting for this dropout rate, to maintain the same power, a total of 137 participants in each of the three cohorts are required for a total of 411 in total.

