### Methods for additional analyses (e.g. subgroup analyses) {20b}

Not applicable as no subgroup analyses are planned though significant interaction effects will be used to suggest a differential effect of treatment across different patient groups.

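### The primary randomised comparison is analysed with P-value-driven covariate selection and several unranked models, and first versus repeated re-presentations is left open, although the trial is sized on one log-rank test

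*Protocol article*

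**What the plan says.** The section on statistical methods for primary and secondary outcomes {20a} sets out how the two active arms are compared with SPP alone:

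- **Models.** "univariate (log rank test) and multivariate Cox proportional hazard shared frailty regression models and multilevel mixed effects parametric models will be used" for the time to re-presentation. No order of priority is given.
- **Events.** The time is counted to a later suicide attempt "and may include multiple representations".
- **Covariates.** "All collected demographic and clinical variables will be considered in the model-building process". Those reaching P ≤ 0.1 "on univariate analysis will be included in all combinations and retained in the model if" P < 0.05.
- **Interactions.** Those judged plausible among the retained variables are then tested. The section on additional analyses {20b} plans no subgroup analyses but adds that "significant interaction effects will be used to suggest a differential effect of treatment across different patient groups".

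Three other places bear on the same analysis. The section on collection of outcomes {18a} names multivariate Cox models only. The primary outcome section speaks of one subsequent attempt and does not mention repeats. The sample size section {14} powers the comparison "by the log rank test in a proportional hazards time-to-event analysis with 80% power at a two-sided significance level of 5"%, but does not call that test the primary analysis.

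**The concern.** Screening candidates on their P-values, trying them in every combination and keeping the significant ones is a recipe for building a prognostic model. In a randomised comparison the treatment effect needs no such search. The search lets the outcome data choose the model, and the reported standard error takes no account of it. The text does not say that treatment is always kept in the model, nor how to choose when several combinations contain only significant terms.

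The unranked list adds a second freedom. A log-rank test on first events, a selected frailty Cox model, a parametric model and a model for repeated events can give different P-values on the same data, and nothing says which one answers the primary question. Two analysts following the section faithfully could reach different conclusions. A retained interaction with treatment would also change what the main treatment coefficient means. At stake is whether the 5% used to size the trial is the error rate of the result finally reported.

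**Working it through.** **1. The plan's own figure.** Inputs from the sample size section: "this represents a decrease from 48 to 24"%, two-sided 5%, 80% power.

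- HR = ln(1 − 0.24) / ln(1 − 0.48) = −0.2744 / −0.6539 = 0.42, which agrees with "equivalent to a hazard ratio of 0.42".
- Freedman's formula: events = (1.960 + 0.842)² × [(1 + 0.4197)/(1 − 0.4197)]² = 7.85 × 5.985 ≈ 47.
- Per group: 47 / (0.48 + 0.24) = 65.3, so 66 per group and 132 in total.

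The stated 132 is reproduced. (Schoenfeld's formula gives 42 events and 59 per group, which does not match.) The sample size therefore belongs to one unadjusted log-rank test on first events.

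**2. What each section fixes.**

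| Section | Test or model | Event | Covariates |
|---|---|---|---|
| Sample size {14} | log-rank | first (implied by the formula) | none |
| Primary outcome measures | not stated | a subsequent attempt | not stated |
| Collection of outcomes {18a} | multivariate Cox | a subsequent attempt | not stated |
| Statistical methods {20a} | log-rank, frailty Cox, multilevel parametric | may be multiple | chosen by P-value |

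**3. Simulation under no treatment effect.** One comparison, 137 per arm, 24 months, dropout 4.5% per month, treatment forced into every model, covariates screened at P ≤ 0.1 and then removed backwards until all have P < 0.05. The number of candidates and their strength are assumptions.

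*Set A*: 1,500 trials per scenario, event rate 48% at 24 months. The Monte Carlo standard error at 5% is √(0.05 × 0.95/1500) = 0.56 points, so the 95% band around 5% is 3.9-6.1%.

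| Candidates | Unadjusted | Selected Cox | Either significant |
|---|---|---|---|
| 20, none prognostic | 4.6% | 5.7% | 6.1% |
| 20, 3 prognostic | 4.1% | 5.3% | 7.3% |
| 30, 3 prognostic | 4.9% | 6.1% | 7.9% |

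*Set B*: 4,000 trials per scenario (standard error 0.34 points), 15 candidates of which 3 are prognostic, and gamma frailty. The hazard implied by 48% at 24 months was multiplied by 1.5. Simplifications: ordinary Cox for frailty Cox, backward elimination for all combinations, an exponential model for the parametric one, and negative binomial for the recurrent-event frailty model.

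| | log HR 0.35 per SD, frailty variance 1 | log HR 0.35, variance 2 | log HR 0.6, variance 1 |
|---|---|---|---|
| Log-rank alone | 4.7% | 5.1% | 5.4% |
| Selected Cox alone | 6.0% | 5.7% | 6.4% |
| Parametric after selection, alone | 6.9% | 7.1% | 8.0% |
| Log-rank or selected Cox | 7.0% | 6.7% | 9.0% |
| … or parametric | 7.9% | 7.9% | 10.2% |
| … or adjusted recurrent-event | 11.0% | 11.4% | 13.0% |
| … or unadjusted recurrent-event | 12.5% | 13.4% | 18.3% |

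**4. Reading the tables.** Selection alone moves the Cox test from about 5% to 5.3-6.4%. The gap from the log-rank is 1.1-1.2 points in set A and 0.6-1.3 points in set B. The larger rates appear only when a significant result from any one of several analyses is allowed to count.

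**The case against.** The best defence has four parts.

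- **The log-rank test can be read as primary.** The sample size rests on it and {20a} names it first, so an unadjusted log-rank supported by an adjusted Cox model is a natural reading. Ranking analyses and naming covariates are also commonly left to an analysis plan. This stands in part. But {18a} names only Cox models, no section says which result decides, and the selection rule is not deferred: it is written out. An analysis plan that followed it would keep the fault, and one that named a single fixed model would contradict it.
- **Selection does little harm by itself.** This stands. The set A rates for the selected Cox model lie within or at the edge of the Monte Carlo band, and set B puts the excess over the log-rank at about one point.
- **The larger rates assume a rule the protocol does not contain.** This also stands. The section says which models will be run, not that any one of them suffices. The fair criticism is that no decision rule is given, and the 6-9% and higher figures describe what that silence permits.
- **First and repeated events are not in flat contradiction.** Correct: the primary outcome section never says first. The matter is left open.

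A reader might go further in two directions that the documents do not support. One is to infer that measures taken after randomisation, such as therapeutic alliance, will be used as covariates. The rule concerns demographic and clinical variables, while the alliance questionnaire is listed among the psychometric measures and therapeutic engagement is a secondary outcome. The other is to put a figure on false interaction findings. The protocol gives no number of tests, limits them to plausible ones among retained variables, and uses them only to suggest a differential effect.

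**Conclusion.** The point holds as a fault in what the protocol fixes. The primary comparison is tied to an outcome-driven choice of covariates, three kinds of analysis are listed with none decisive, and the event definition is open, while the sample size assumes one first-event log-rank test at two-sided 5%.

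A reader might infer that the 5% level is certainly lost. The documents do not support that. A log-rank test declared as the sole primary test would keep about 5% for a single comparison (4.7-5.4% in set B), and selection alone gives 5.3-6.4%. Only if success may rest on either the log-rank or the selected Cox model does the rate reach about 6-9%. It reaches 7.9-10.2% with the parametric model added, and 11.0-18.3% with recurrent-event models as well. All these figures depend on assumed covariate numbers (15 to 30), prognostic strength and frailty variance, and on the stated simplifications. The two comparisons with SPP and the additional primary proportions are outside them.

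**What to change.** In {20a}, name one primary analysis:

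- one event definition, time to first re-presentation with a suicide attempt, which matches the log-rank sizing;
- one test or model, with treatment always included;
- either no covariates or a short list of baseline covariates fixed before outcome data are seen.

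Delete the P-value screening for that analysis. Label the frailty and multiple-event models, the parametric models, the covariate exploration and the interactions in {20a} and {20b} as sensitivity or exploratory, and align the model named in {18a}.

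The cost is wording only. The 66 per group before dropout is unchanged, since it was already calculated for the log-rank test. The trial status section reports 12 participants recruited, so at that stage the change could be made with very little outcome data accrued.

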### Interim analyses {21b}

Not applicable; no interim analyses will be conducted for this study.

### Methods for additional analyses (e.g. subgroup analyses) {20b}

Not applicable as no subgroup analyses are planned though significant interaction effects will be used to suggest a differential effect of treatment across different patient groups.

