### Interventions

#### Explanation for the choice of comparators {6b}

Both ASSIP and the Brief CBT for Suicide Prevention have an existing evidence base and both have been shown to be cost-effective in their own right [17, 34]. In addition, the effect and cost-effectiveness of both interventions are not known when delivered in the context of a clinical Suicide Prevention Pathway, which has, itself, been shown to reduce representations with suicide attempts compared to traditional treatment [35]. Different interventions may work for different people (e.g. video-assisted narrative vs. traditional approach to identifying core beliefs driving behaviour), so it is important for the field to know which works best with whom.

ASSIP is an evidence-based intervention for reducing suicidal behaviour, while also reducing healthcare costs [36]. In the seminal randomised controlled trial (RCT) of ASSIP, conducted in Switzerland by the developers of the intervention, the ASSIP treatment, which added one session of risk assessment to treatment as usual, reduced suicide reattempts dramatically compared to treatment as usual. Over a 24-month period, individuals in the treatment group had an 80% risk reduction for suicide reattempt and an average of 72% fewer hospital days than control patients over 24 months [17, 37, 38].

CBT can challenge maladaptive beliefs, improve problem-solving skills, and social competence. Systematic reviews and meta-analyses have found CBT to be highly effective in reducing suicidal behaviour [34]. Denchev et al. found CBT to be a cost-effective intervention that reduced suicide risk among patients who presented to general hospital EDs [39]. A systematic review of the evidence on CBT concluded that it was effective in reducing self-harm behaviour and repeated suicide attempts in fewer than 10 individual sessions in patients who had made a previous suicide attempt [40]. Brief CBT for suicide prevention compared to conventional CBT has the advantage of being more cost-effective and time-efficient [24].

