### Data collection and management

#### Plans for assessment and collection of outcomes {18a}

Each person who presents to Gold Coast Health is assigned a unique identifying, or UR, number. The Emergency Information System at Gold Coast Health (viz., FirstNet database) records all ED presentations. The ED presentations will be interrogated for the UR number of all study participants, and any presentation within 24 months of an initial presentation will be reviewed for evidence of suicidality. Multivariate Cox proportional hazard regression models will be used to analyse time to re-presentation for a suicide attempt. Time to suicide attempt is measured by calculating the total number of days from the initial presentation (not including days of admission for some consumers with medical and/or psychiatric admission) to the re-presenting date for a subsequent suicide attempt.

For secondary outcomes, data are collected by the RA at five time points: (1) baseline, (2) end of CBT or ASSIP interventions, (3) 6 months, (4) 12 months, and (5) 24 months from baseline. At baseline, demographic data and psychometric data are collected in person or via the telephone with the RA, as outlined below. At end of treatment and 6, 12, and 24 months, psychometric data are collected. Therapeutic alliance is assessed at the completion of the interventions. Cost comparisons will be based on service information regularly collated by GCMHSS and ED (e.g. contact hours, bed stays, ED visits). Study completion will be analysed post hoc, as a secondary outcome.
i)Demographic data: includes age, gender, method of suicide attempt, employment status, education history, place of residence, living situation, marriage status, family contact, known diagnoses and co-occurring conditions (e.g. drug and alcohol use), and history of service provision, including use of psychological interventions

It is anticipated that a number of people within the study population will be from specific cultural groups, who may also be high-risk populations, such as Aboriginal and Torres Strait Islander people, people from cultural and linguistically diverse (CALD) communities, people who identify as LGBTQI, older persons (aged over 60 years), and young people (aged 16–18 years). Questions are included to enable the identification of these specific target population subgroups.

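### Treatment interactions are tested only for variables that survive a main-effect screen, so effect modifiers that cancel across arms can go untested

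*Protocol article*

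**What the plan says.** The rule is spread over two sections of the protocol article.

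- **Statistical methods {20a}.** "All collected demographic and clinical variables will be considered in the model-building process". Those with univariate P ≤ 0.1 "will be included in all combinations and retained in the model if" P < 0.05. Then: "Plausible interactions of retained variables will be tested".
- **Additional analyses {20b}.** "Not applicable as no subgroup analyses are planned", yet "significant interaction effects will be used to suggest a differential effect of treatment across different patient groups".

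The section on the choice of comparators {6b} notes that different therapies may suit different people, "so it is important for the field to know which works best with whom".

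The article gives no number of interactions and no significance level for them. It does not say whether the two therapy arms are tested jointly or separately, and it does not define plausible. An analysis plan that is not shown may settle those details. The point here is the rule that is stated: retention on main effect comes before any interaction test.

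**The concern.** A main-effect screen and an interaction test answer different questions. The screen averages a variable's association with re-presentation over three equal arms. A variable can change the treatment effect a great deal and still show little average association. Two patterns are natural in this trial:

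- one group does better on ASSIP and the other on CBT, so the effects offset each other;
- a group at higher risk under SPP gains more from therapy, so its excess risk in one third of the sample is offset in the other two thirds.

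The first pattern is the matching question raised under {6b}. Under the stated rule such a variable would usually be dropped and its interaction never examined. For variables that do get through, a significant interaction is to be used to suggest a differential effect, and no count of tests is given against which to judge it.

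**Working it through.** **Inputs from the protocol article.** Three arms at 1:1:1; 137 per arm; two-year re-presentation of 48% v 24%; HR 0.42; dropout of 4.5% per month; screening thresholds P ≤ 0.1 and P < 0.05. The 5% level is stated for the log rank test ("with 80% power at a two-sided significance level of 5" per cent) and P < 0.05 for retaining covariates. Applying 5% to interactions is an assumption.

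**The plan's own figure.** ln(0.76)/ln(0.52) = 0.42. Freedman's formula gives 47–48 events; 47/0.36 = 131 and 48/0.36 = 133, which bracket the stated 132 (two groups of 66). The event rates and hazard ratio are therefore a sound base. The article gives no figure for interactions.

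**Why cancellation matters.** Let g be the variable's log HR under SPP, and a and c its interactions with ASSIP and CBT. Averaged over three equal arms, its association is roughly g + (a + c)/3. This is approximate, because the SPP arm contributes more events.

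- Opposite modification: 0 + (−1 + 1)/3 = 0.
- Therapy HR 0.25 v 0.70, first group at 2× the SPP hazard: ln 2 + (2/3) × ln(0.25/0.70) = 0.693 − 0.686 = 0.007.
- Same HRs at 1×: −0.686. At 3×: 1.099 − 0.686 = 0.412.

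**Simulated retention and power.** These use a balanced binary variable, 137 per arm and 4.5% monthly dropout. Retention means univariate P ≤ 0.1, then P < 0.05 in a Cox model with treatment. Direct power is for a joint 2-df interaction test at 5%. All effect sizes are assumptions. In the opposite-direction case both therapies average HR 0.42 (log −0.87), so each has HR exp(−1.37) = 0.25 in one half and exp(−0.37) = 0.69 in the other, reversed between therapies.

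| Assumed modifier (log HR unless stated) | Average association | Retained | Direct power | Retained and significant |
|---|---|---|---|---|
| ASSIP −1, CBT +1 | 0 | 4% | 81% | 4% |
| SPP +0.6, both therapies −1.2 | −0.20 | 4% | 67% | 3% |
| HR 0.25 v 0.70, 2× SPP hazard | 0.007 | 12% | 52% | not tabulated |
| ASSIP only −1.2 | −0.40 | 28% | 49% | 13% |
| Both −0.87, no SPP effect | −0.58 | 48% | 35% | 17% |
| HR 0.25 v 0.70, 1× or 3× SPP hazard | −0.69 or 0.41 | 65–74% | not tabulated | not tabulated |
| Both −1.74, no SPP effect | −1.16 | 98% | 93% | 90.5% |

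The loss is near total where effects cancel and slight where a strong effect runs the same way in both therapies.

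**False interactions.** For k retained variables with no true interaction, one 2-df test each gives 1 − 0.95^k: 14.3% for k = 3 and 22.6% for k = 5. Two separate contrasts sharing the SPP arm (correlation 0.5) give 9.1% per variable, so 1 − (1 − 0.091)^k: 24.8% and 37.9%. Passing 20 assumed binary candidates through the full screen, with every retained variable tested, gives:

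| Truly prognostic (log HR 0.6 each) | Mean retained | Joint 2-df test | Separate contrasts |
|---|---|---|---|
| 0 | 0.9 | 2% | 7% |
| 3 | 2.9 | 12% | 22% |
| 5 | 4.4 | 19% | 35% |
| 8 | 6.5 | 30% | 51% |

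Simulation error is at most about ±5 points. The demographic list in {18a} ("includes age, gender, method of suicide attempt, employment status, education history, place of residence, living situation, marriage status, family contact, known diagnoses and co-occurring conditions", and more) names about 13 items, so 20 candidates is an assumption.

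**The case against.** The strongest reply is that the interaction analysis is modest by design. The objectives are the two comparisons with SPP, and no hypothesis concerns effect modification. The matching remark is background to the choice of comparators. No subgroup analyses are planned, the interactions are limited to plausible ones, and they only suggest a difference. A list of interactions, the form of the test and any multiplicity rule could properly sit in an analysis plan.

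Much of this stands. It sets the weight of the point, and the absence of a list is no finding. It does not rescue the gate: plausibility is applied only after retention, and cautious wording cannot help a modifier that is never tested. An analysis plan would have to depart from the stated rule to repair it.

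The results also depend on the scenario. With therapy HRs of 0.25 v 0.70, the univariate screen alone passes the modifier in 18% of trials at 2× SPP hazard, but in 77% at 1×, 79% at 3× and 99.7% at 0.67×. The 2× case sits close to exact cancellation.

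A reader might infer more than the document supports:

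- **That false interactions will appear in a third or more of trials.** This needs about 8 variables with joint tests (33.7%) or about 5 with separate contrasts (37.9%). The document fixes neither, and the screen itself reduces the number of tests.
- **That any P < 0.05 will be declared a differential effect.** {20b} says only significant, and uses it to suggest.
- **That a screen with no finding will be reported as no differential effect.** Nothing says so.
- **That the contrast is as stark as 92% v 7%.** That power comes from a pooled-therapy 1-df test with no dropout. It is not the power of the joint test under the plan's own dropout.

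**Conclusion.** The concern holds in a limited form. Taken together, {20a} and {20b} make main-effect retention the gate to the interaction test, and that gate can discard true modifiers whose effects cancel across arms. Under the assumed effects and the plan's dropout, retention is about 4% against about 80% direct power for opposite ASSIP and CBT modification. It is about 12% against 52% for a higher-risk group that benefits more. Modifiers that do not cancel are often retained, so the claim is that the rule can miss modifiers, not that it misses them in general.

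The false-interaction rate cannot be read from the document. The range of about 2% to 51% depends on how many variables are prognostic and whether the arms are tested jointly or separately. It also assumes 20 candidates, a 5% level and testing of every retained variable; limiting tests to plausible interactions would lower it. The point affects the exploratory conclusions about who benefits from which therapy, not the comparisons with SPP.

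**What to change.** In {20a}, stop making treatment interactions conditional on retention. Name a short set of baseline variables already collected; age band, gender and baseline C-SSRS severity are possible examples, and the choice is the trial team's. Test each in a model containing treatment, that variable and their interaction, with one joint 2-df test, whether or not the variable passed the covariate screen.

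In {20b}, call these analyses exploratory, report interaction hazard ratios with 95% confidence intervals and the number of tests done, and state that a single significant result will not be read as evidence of a differential effect.

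The cost is wording and a few extra models; no new data or participants are needed. Power per interaction stays modest, about 52% in the higher-risk scenario. With Holm adjustment over three variables, the first step is tested at 0.05/3 and power there falls to about 33%. That adjustment is therefore optional for an exploratory analysis, provided the number of tests is reported.
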